## Abstract

Heart failure is a prevalent condition and a frequent cause of hospital readmissions and poor quality of life. Teleconsultation support from cardiologists to primary care physicians managing patients with heart failure may improve care, but the effect on patient-relevant outcomes is unclear. We aim to evaluate whether collaboration through a novel teleconsultation platform in the Brazilian Heart Insufficiency with Telemedicine (BRAHIT) project, tested on a previous feasibility study, can improve patient-relevant outcomes. We will conduct a parallel-group, two-arm, cluster-randomised superiority trial with a 1:1 allocation ratio, with primary care practices from Rio de Janeiro as clusters. Physicians from the intervention group practices will receive teleconsultation support from a cardiologist to assist patients discharged from hospitals after admission for heart failure. In contrast, physicians from the control group practices will perform usual care. We will include 10 patients per each of the 80 enrolled practices (n = 800). The primary outcome will be a composite of mortality and hospital admissions after six months. Secondary outcomes will be adverse events, symptoms frequency, quality of life, and primary care physicians’ compliance with treatment guidelines. We hypothesise that teleconsulting support will improve patient outcomes.

## 1. Introduction

Heart failure is a common outcome of many cardiovascular and metabolic diseases, leading to a high disease burden, frequent hospital admissions, and poor quality of life [1]. The adequate management of patients with heart failure relies on care integration among healthcare sectors [2,3,4], including primary care, especially in low- and middle-income countries, where it is known to reduce admission rates [5,6,7]. One recommended collaboration strategy is teleconsultation (e-consultation) support between healthcare providers, usually from subspecialists to primary care physicians [8,9,10].

Previous observational studies have shown that teleconsultation support enhances primary care physicians’ confidence, capacity, and satisfaction rates [8,11]. In cardiology, Olayiwola et al. [12] suggested that teleconsultation may increase access to cardiology evaluation while reducing in-person referrals. On the other hand, two extensive reviews [13,14] showed that no study clearly demonstrated the impact of provider-to-provider communication using technology on patient-relevant outcomes such as mortality, hospital admissions, or quality of life.

Although the use of remote communication tools between providers is already recommended by the World Health Organisation [10], one must ascertain whether this technology is effective and impacts patient-relevant outcomes to guide rational stakeholders’ investment in teleconsultation services.

In this study, we aim to test the effects of a teleconsultation service provided by the BRAHIT project, a Danish-Brazilian academic collaboration, on heart failure management in primary care practices in Rio de Janeiro, Brazil. We will perform a cluster randomised trial to account for the practice-level intervention effect. The primary outcome will be a composite of hospital readmission and mortality. Secondary outcomes will be serious adverse events, patient-reported quality of life, and frequency of symptoms. The physicians’ compliance with treatment guidelines will be reported as an exploratory outcome.

## 2. Materials and Methods

### 2.1. Study Design

We will conduct a parallel-group, two-arm, superiority cluster-randomised controlled trial with a 1:1 allocation ratio. 

### 2.2. Study Setting

The study setting is the primary healthcare network of Rio de Janeiro, the second-largest city in Brazil, with 6,320,446 inhabitants and a free public health system [SUS]. There are 236 primary care practices with 1307 health teams composed of one physician, one nurse, one nursing technician, and four to six community health agents delivering comprehensive care for inhabitants of a defined area, according to the family health strategy model [15,16,17]. Besides this conformation, there are also practices where primary care is not entirely delivered following this model, but by physicians and allied professionals who are not integrated into the team. 

The population can access the health system at their corresponding practice, pre-hospital facilities (*Unidade de Pronto Atendimento*—UPA), or the emergency rooms of secondary hospitals. When a patient in primary care needs further evaluation in an acute setting, the patient is transported by ambulance to a pre-hospital facility or an emergency room in a secondary hospital, where they can remain in observation or be admitted to the ward or intensive care unit. Tertiary hospitals, reserved for high-complexity cases, are accessed through regulation systems managed by the state administration.

Data on heart failure epidemiology and management in Rio de Janeiro is scarce, usually found only in surveys and academic publications. If we estimate a 1% prevalence in the general population (63,204 people living with heart failure), an admission rate of 24.9% and a mortality rate of 24% per year in this specific population, as found in the literature [18,19,20], one could expect around 15,378 admissions and 3777 deaths per year in the city. 

We started the Danish-Brazilian BRAHIT project in 2019 using telemedicine tools to improve primary care in heart failure. In a single-arm feasibility test, we assigned cardiologists to support primary care physicians from one practice on heart failure case management via videoconference meetings at physicians’ requests. Twenty-four cases were discussed through videoconference. This model was used until June 2021, when it was scaled up and adapted to a web-based platform, where 40 new patients were included from 11 other primary care practices and specialised hospital-based homecare teams. Data from the 64 cases revealed some improvement opportunities. According to the physicians’ reports provided with the teleconsultation requests, most patients were in poor physical status, with 51% experiencing NYHA (New York Heart Association) class III or IV symptoms. In addition, 67% had at least 2 signs or symptoms of poor clinical control, i.e., dyspnoea, dizziness, fatigue, sleeping problems, leg swelling, pulmonary rales, or jugular distension. Essential recommended therapy was prescribed for only 19% of patients, and only 14% had their vital signs adjusted within the recommended limits (blood pressure < 120 × 80 mmHg and heart rate < 80 bpm).

### 2.3. Eligibility

#### 2.3.1. Inclusion Criteria for Patients

Patients over 18 years old with a diagnosis of heart failure who have been discharged within the past month from a public hospital or pre-hospital facility and are registered in a public primary care practice.

#### 2.3.2. Inclusion Criteria for Study Centres and Staff

All 236 primary care practices from Rio de Janeiro municipality and their physicians are eligible for the study. According to the above criteria, we will include primary care practices progressively, determined by where the eligible patients are registered. 

#### 2.3.3. Exclusion Criteria

We will exclude participants who refuse to participate in the study, patients where heart failure is excluded as a diagnosis after the first contact with primary care or teleconsultation, and patients without a defined reference physician to receive the teleconsultation intervention, due to physician shortage. We will also exclude from the study the practices and patients involved in the feasibility test.

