### 2.7. Assignment of Interventions

#### 2.7.1. Allocation—Sequence Generation

Primary care practices from Rio will be stratified into four strata according to two factors, each having two levels: the family health strategy model running exclusively in the practice (presence or absence) and the Social Development Index (≤0.60 or >0.60). [24]. The research team has concluded that both factors are important determinants of the work process quality and patient outcomes, respectively [5,25,26].

We will randomise practices within each stratum after recruitment to control or intervention groups, using a computerised random number generator on a simple 1:1 allocation ratio to increase homogeneity between the groups. Once we randomise the practices, we will allocate the patients and apply the intervention of the physician or follow-up, depending on the group.

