### 2.9. Data Retention

Once a patient and the corresponding physician and practice are recruited, the research team will apply and monitor the retention rate. We will disseminate the project in social media to increase awareness, adhesion, and retention of the primary care physicians in the project. 

In the intervention group, the teleconsulting team will promptly respond to physicians’ requests, use communication tools that best suit their routine, and consider the practice and patient’s context to deliver a feasible teleconsultation. Those features were assessed during the feasibility test, with favourable results. These factors will increase participant and data retention. A dedicated researcher will monitor the teleconsulting process, ensuring that physicians evenly receive high-quality support. Discontinuation of participants’ adherence after enrolment will be used for censoring and analysed following an intention-to-treat principle.

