#### 2.11.2. General Analysis

We will conduct all analyses according to the intention-to-treat principle, where we analyse data as randomised regardless of adherence to the research protocol. An additional per-protocol analysis will be performed for exploratory reasons if the drop-out rate exceeds 5% of the total trial population. We will assess whether the statistical and clinical significance thresholds apply [30], based on the estimated intervention effects and power estimations used in the sample size.

We will base our main conclusions on the primary outcome, following the intention-to-treat principle, assuming a type 1 error threshold of 5% (*p* < 0.05), with the relative risk and confidence intervals (CIs) calculated at the 95% level and a type 2 error threshold of 0.2 (80% statistical power).

Regression analyses will be adjusted for the factors used in the randomisation (the exclusive presence of the family health strategy model in the practice and the social development index stratum), assessing for significant interactions between them and the outcome variables. We will consider the results of secondary or exploratory outcomes as hypothesis-generating only. No subgroup analysis besides the one using the stratification factors is planned; if executed, these results will also be hypothesis-generating only.

Categorical variables will be described as absolute and relative frequencies, and continuous variables as medians (interquartile range) or means (standard deviation) according to the distribution of the variable. Missing data will be handled according to Jakobsen’s recommendations [31]; briefly, we will include participants in the primary analysis of all outcomes and anticipate a less than 5% missing value rate. We will then perform a secondary analysis considering the use of multiple imputations and present best-worst and worst-best case scenarios if it is not valid to ignore missing data.

To account for clustering within each primary care practice, all outcomes will be analysed using generalised estimating equation methods (GEE) [32]. All analyses will additionally be adjusted for the stratification variables used in the randomisation. The software R (R Foundation for Statistical Computing, Vienna, Austria; version x64 3.6.0, including the package “geepack” for GEE) [33] and STATA will be used for statistical analysis.

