## Figures and Tables

**Figure 1 ijerph-20-05933-f001:**
[figure not shown]
Study workflow.

**Table 1 ijerph-20-05933-t001:** Participant Timeline.

Enrolment	T_−1_	T_0_	T_6_ (Close-Out)
General practice stratification and randomisation	X		
Patient eligibility screening using municipality data	X		
Invitation to participate (patient)	X		
Invitation to participate (physician)	X		
Informed consent (patient and physician)	X		
Patient allocation according to practice randomisation		X	
Intervention			
Intervention group		Teleconsultation support for the practice’s physicians (first contact and on demand)	
Control group		Usual care with follow-up of outcomes	
Assessments		T_0_	T_6_ (close-out)
1—Readmissions and Mortality (reports)			X
2—Days Alive Out of Hospital (DAOH)			X
3—Frequency of Serious Adverse Events			X
4—Symptoms Frequency and Severity		X	X
5—Quality of Life		X	X
6—Adherence to Prescribing Guidelines		X	X

**Table 2 ijerph-20-05933-t002:** Baseline Variables.

N	Variable	Field Type	Choices, Calculations, or Labels
Physician Variables—direct inquiry			
1	Name	Text	-
2	Social Identification Number (CPF)	Text	-
2	Completed years since graduation	Number	-
3	Specialisation	Option	Any/Family Medicine/Other
4	Completed years in primary care	Number	-
5	Completed years in the current practice	Number	-
6	Enrolled in a residency program	Options	No/Preceptor/1st year Resident/2nd year Resident/3rd year Resident/Program
Patient Variables—primary care electronic health record report			
1	Name	Text	-
2	Social identification number (CPF)	Text	-
3	National Health System identification number (CNS)	Text	-
4	Primary care practice	Text	
5	Gender	Options	Feminine/Masculine/Nonbinary
6	Race	Options	White/Black/Brown/Other
7	Birth date	Date	-
8	Weight (Kg)	Number	-
9	Height (cm)	Number	-
10	NYHA status	Options	1 to 4
11	Systolic blood pressure	Number	-
12	Diastolic blood pressure	Number	-
13	Heart rate	Number	-
14	Dyspnoea	Option	Yes/No
15	Leg Swelling	Option	Yes/No
16	Dizziness	Option	Yes/No
17	Fatigue	Option	Yes/No
18	Orthopnoea or paroxysmal nocturnal dyspnoea	Option	Yes/No
19	Syncope	Option	Yes/No
20	Typical chest pain	Option	Yes/No
21	Jugular vein distension	Option	Yes/No
22	Pulmonary rales	Option	Yes/No
23	ACE-I (names)	Option	ACE-I names
24	ACE-I dose	Number	-
25	ARB (names)	Option	ARB names
26	ARB dose	Number	-
27	Beta-blockers (names)	Option	BB Names
28	Beta-blockers dose	Number	-
29	Spironolactone	Option	Yes/No
30	Spironolactone dose	Number	-

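### The diagnostic exclusion in Section 2.3.3 can act through teleconsultation, which occurs only in the intervention arm and after allocation, and so contradicts the stated intention-to-treat analysis

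*Protocol article*

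**What the plan says.** Section 2.3.3 lists among the exclusions "patients where heart failure is excluded as a diagnosis after the first contact with primary care or teleconsultation".

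The Abstract describes the arms: "Physicians from the intervention group practices will receive teleconsultation support from a cardiologist", whereas "physicians from the control group practices will perform usual care". Section 2.7.1 gives the order of events: "Once we randomise the practices, we will allocate the patients and apply the intervention of the physician or follow-up, depending on the group". Table 1 agrees. It puts eligibility screening and consent at T−1 and patient allocation at T0, and its T0 entry for the intervention group reads "Teleconsultation support for the practice’s physicians (first contact and on demand".

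Section 2.11.2 sets the analysis principle: "We will conduct all analyses according to the intention-to-treat principle, where we analyse data as randomised regardless of adherence to the research protocol". Section 2.9 says that discontinuation of participants' "adherence after enrolment will be used for censoring and analysed following an intention-to-treat principle".

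**The concern.** Both arms enter through the same door: a registered heart failure code in the municipal discharge data (Section 2.6). After allocation, only intervention patients have a cardiologist look at the case, and Section 2.3.3 makes the outcome of that look a ground for exclusion. Section 2.8 concedes that care providers cannot be blinded, so those whose judgement triggers the exclusion know the arm.

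A patient removed for a reason that the intervention itself generates is not analysed as randomised. The patients left in the intervention arm are then a more selected group than the controls, and the primary relative risk mixes that selection with any treatment effect. Adjusting for the two stratification factors does not repair this.

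The Section 2.9 sentence is a second, smaller conflict. Censoring at discontinued adherence does not fit an analysis that ignores adherence. Nor does it have a defined role in a six-month yes/no composite analysed by GEE with a relative risk.

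**Working it through.** **The plan's own figure.** Inputs from Section 2.11.1: control risk 40.1%, effect 30%, ICC 0.05, 10 patients per cluster, 5% type I error, 80% power. Reading 30% as a relative reduction gives 0.401 × 0.7 = 0.2807. The two-sided two-proportion formula without continuity correction gives 243 per arm. The design effect is 1 + (10 − 1) × 0.05 = 1.45. Then 243 × 1.45 = 352.4 per arm, or 36 clusters of 10 per arm and 72 in all, which is the stated minimum. The concern therefore does not rest on the sample size.

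**Which exclusions are one-sided.**
- First contact with primary care: available in both arms.
- Teleconsultation: intervention arm only, after allocation (Abstract, Section 2.7.1, Table 1).

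The asymmetry is thus the excess: diagnoses that the cardiologist refutes and primary care does not.

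**Size of the bias with no true effect.** Let q be that excess, as a share of the patients who would otherwise be analysed. Let k be the event risk of refuted patients divided by the risk x of true cases. Controls have risk x(1 − q + qk). The intervention arm, with refuted patients removed, has risk x. Hence

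RR = 1 / (1 − q + qk).

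For q = 10%: k = 0.5 gives 1/0.95 = 1.053, and k = 1.5 gives 1/1.05 = 0.952. The documents give neither q nor k, so the values below are assumptions. With 400 patients per arm:

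| Excess removed, q | Patients | RR, k = 0.5 | RR, k = 1.5 | Type I error, k = 0.5 |
|---|---|---|---|---|
| 2% | 8 | 1.01 | 0.99 | 5.1% |
| 5% | 20 | 1.03 | 0.98 | 5.7% |
| 10% | 40 | 1.05 | 0.95 | 7.8% |
| 20% | 80 | 1.11 | 0.91 | 17.0% |

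The type I error column uses a normal approximation with 40.1% control risk and an effective size of 400/1.45 = 276 per arm, reduced by q in the intervention arm. For example, at q = 10% the intervention risk is 0.401/0.95 = 0.4221. The spurious difference of 0.0211 has standard error 0.0430, a shift of 0.49, which gives a two-sided rejection rate of 7.8%.

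The 40.1% is an annual figure and the outcome is at six months. A constant hazard would give 1 − √(1 − 0.401) = 22.6%. The relative risks do not change. Type I error at k = 0.5 becomes 6.2% for 10% removed and 10.0% for 20%.

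**Power at the planned effect.** With 80 clusters, 40.1% against 28.07% and no differential removal, power is 84.8%. With k = 0.5 the observed intervention risk rises to 28.07%/(1 − q + qk), which is 29.55% at q = 10%. Power falls to 78.9%, 71.7% and 53.8% for 5%, 10% and 20% removed.

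**Direction.** Section 3.2 counts a stay as a readmission only if it is because of heart failure, but counts death from any cause. Patients without heart failure should have fewer such readmissions. That makes k below 1, and so bias against the intervention, the more plausible case. The all-cause death component means it is not certain.

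**The case against.** The best defence is that the rule is not wholly one-sided and may seldom be used. Controls can also be excluded after their first primary care contact. Entry already requires a heart failure code and, under Section 2.4, admission for decompensated heart failure as the primary discharge diagnosis, so few diagnoses may be left for a cardiologist to refute. At 2% the effect is negligible. This stands, and it limits the size of the bias. It does not remove the contradiction. Section 5 itself cites difficulties with diagnosis in primary care and suggests a competence gap among its physicians, so a specialist can be expected to refute some diagnoses that primary care does not.

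Three stronger readings are not supported:

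- A reader might infer that controls keep all their misdiagnosed patients. They do not, because the primary care route removes some of them too.
- A reader might infer from Section 2.9 that outcomes are lost in proportion to physicians' non-use of the platform, which Section 4 names as the main risk. Section 2.9 concerns participants' adherence, does not say that later events are dropped, and itself invokes intention-to-treat. Sections 2.11.2 and 5 state that principle whatever the adherence. What is shown is conflicting wording.
- A reader might add the exclusion of "patients without a defined reference physician to receive the teleconsultation intervention, due to physician shortage" as another one-sided rule. It would be one-sided only if applied after allocation. Section 2.6 has the physician accept before the patient is invited, and Table 1 puts physician consent at T−1, so this check appears to come first.

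**Conclusion.** The exclusion rule is wrong as written. Followed literally, it removes allocated patients through a route open in one arm only, and the plan cannot also claim to analyse as randomised. That conclusion needs no assumption about rates.

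The size does need assumptions. Over an excess removal of 2% to 20%, the null relative risk ranges from 1.01 to 1.11 at half the event risk, and from 0.99 to 0.91 at 1.5 times. At 10% the distortion is about 0.05, roughly one sixth of the planned 30% reduction (0.05/0.30). If few diagnoses are refuted it is trivial. No particular size can be claimed from the documents.

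The censoring sentence in Section 2.9 is a secondary point: a contradiction to be reconciled, with no demonstrated loss of outcomes.

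**What to change.** **Section 2.3.3.** Delete the teleconsultation route and any other diagnostic exclusion that takes effect after allocation. Rest eligibility on the discharge code and an identified physician, both settled before allocation and in the same way in each arm. Sections 2.4 and 2.6 already contain most of this.

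**Section 2.11.2.** State that every allocated patient enters the primary analysis. Use refuted diagnosis only in a labelled sensitivity analysis.

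**Section 2.9.** Replace the censoring sentence with a statement that all allocated patients are followed in the municipal admission and mortality reports to six months regardless of adherence, unless consent to data use is withdrawn. Confine any censoring to the exploratory per-protocol analysis.

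**Cost.** Wording only, since Section 3.1 already draws admissions and deaths from those reports. The downside is slight dilution from misdiagnosed patients kept in both arms. As an illustration, suppose 10% are misdiagnosed with half the event risk, the intervention does nothing for them, and the relative risk is 0.70 in true cases. The overall relative risk is then (0.9 × 0.70 + 0.1 × 0.5)/(0.9 + 0.1 × 0.5) = 0.68/0.95 = 0.72.

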### 2.4. Interventions

The intervention comprises teleconsultation support from a cardiologist to a primary care physician in reference to the case management of a patient included in the study.

Based on the primary discharge diagnosis, the research team will collect admissions due to decompensated heart failure, from monthly reports provided by the municipality. We will invite the eligible patients and their corresponding primary care physicians to participate in the study. Invitations will be issued by texting, telephone call, or in-person contact, and signed informed consent forms from patients and physicians will be obtained. 

After the patient and physician agree to participate, we will sign up the physician on a secure online platform for teleconsultation hosted on the research team’s web domain. Through a digital form, they will provide data about professional identification, contact information, patient demographics, and clinical data. They will use the practice’s computers or their own devices to connect and discuss the case with the teleconsulting cardiologist.

The consultant cardiologists must be active National Institute of Cardiology staff members and perform academic activities in undergraduate or graduate programs. They are trained in heart failure management and in using the project’s digital tools. They will use the computers from the research department at the National Institute of Cardiology (INC) or personal devices to access the platform at least twice a week on working days and give feedback to primary care physicians about clinical management. 

The interactions may happen asynchronously, via the teleconsultation platform’s message interface or WhatsApp© texting, or synchronously, by phone call or videoconference, at the physicians’ preference. The duration of the teleconsultation period will depend on the physician’s judgment. This approach is designed to ensure the pragmatism of the intervention [21,22]. Besides the changes recommended by the teleconsultation, all patients will receive the usual care planned by their practice teams, including physician and nurse consultations, prevention measures, oral health treatment, and community agent follow-up visits.

